### Statistical analysis

2.10

All analyses will be prespecified and performed after prospective database lock. The primary analysis population will include participants with two blinded bedside CRS-R assessments, usable EEG according to protocol, and an adjudicated reference score. A feasibility population will include all consented participants.

Baseline characteristics will be summarized as mean and standard deviation or median and interquartile range for continuous variables, and as counts and percentages for categorical variables. The primary analysis will summarize *D*_*i*_ and test whether the mean participant-level error reduction differs from zero using a paired test appropriate to the empirical distribution. A linear mixed-effects model with participant as a random effect and method and rater as fixed effects will be used as a secondary sensitivity analysis to estimate rater-level effects. Intraclass correlation coefficients, mean absolute error, root mean square error, and Bland-Altman plots will be reported with 95% confidence intervals.

Diagnostic-category agreement will be assessed with weighted kappa, macro-averaged F1-score, sensitivity, specificity, and confusion matrices using the mapping rules in Table 1. Subscale-level performance will be assessed using ordinal agreement metrics, weighted kappa, and subscale-specific absolute error. Inter-rater variability before and after AI-assisted standardization will be compared using paired tests and mixed-effects models. The uncertainty module will be evaluated by testing whether high-uncertainty cases are enriched for large scoring error, rater disagreement, or reference-standard disagreement.

Confidence intervals for primary and major secondary metrics will be estimated using participant-level bootstrap resampling. Prespecified subgroup analyses will explore model performance across etiology, chronicity, tracheostomy status, severe motor impairment, and recent sedative exposure. Sensitivity analyses will exclude participants with substantial clinical changes between ratings, cases exceeding target timing windows, and cases with major sedation or airway changes during the assessment episode. A reduced-feature inference mode using report-level EEG variables only will also be tested.

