### Outcome measures

2.7

The primary outcome is the participant-level reduction in absolute CRS-R total-score error after AI-assisted standardization. For rater *j* of participant *i*, raw and AI-standardized absolute error, and participant-level paired difference are defined in Equations 1, 2, and3, respectively.

$$\begin{array}{l} \Delta_{ij}^{\text{raw}}=|T_{ij}^{\text{raw}}-T_{i}^{\text{ref}}|, \end{array}$$
(1)

$$\begin{array}{l} \Delta_{ij}^{\text{AI}}=|{\hat{T}}_{ij}-T_{i}^{\text{ref}}|, \end{array}$$
(2)

where $T_{i}^{\text{ref}}$ is the adjudicated reference total score.

The participant-level paired difference will be:

$$\begin{array}{l} D_{i}=\frac{1}{2}\overset{2}{\underset{j=1}{\sum }}\left(\Delta_{ij}^{\text{raw}}-\Delta_{ij}^{\text{AI}}\right). \end{array}$$
(3)

The primary analysis will test whether the mean of *D*_*i*_ differs from zero, with positive values indicating error reduction after AI-assisted standardization. This definition aligns the endpoint with the participant-level recruitment target while preserving both rater-specific observations.

Secondary outcomes include mean absolute error, root mean square error, agreement between AI-standardized and reference diagnostic category, agreement between standardized and reference subscale scores, reduction in inter-rater variability, sensitivity and specificity for detection of MCS and emergence from MCS, macro-averaged F1-score, uncertainty-flag performance, workflow feasibility, and exploratory consciousness improvement at day 14. Consciousness improvement will be defined as at least one ordered diagnostic-category improvement by day 14 compared with baseline. CRS-R total-score change at day 14 will be analyzed as a sensitivity metric. Discharge status and discharge timing will be reported descriptively rather than used as a primary prognostic time point.

Inter-rater variability for raw and AI-standardized total scores is calculated as specified in Equations 4 and 5.

$$\begin{array}{l} V_{i}^{\text{raw}}=|T_{i1}^{\text{raw}}-T_{i2}^{\text{raw}}|, \end{array}$$
(4)

$$\begin{array}{l} V_{i}^{\text{AI}}=|{\hat{T}}_{i1}-{\hat{T}}_{i2}|. \end{array}$$
(5)

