### Data management and software environment

2.12

Study data will be entered into a secured electronic case report form with role-based access control and an audit trail. Personal identifiers will be stored separately from the analytic dataset. Each participant will be assigned a study identification code linking behavioral, clinical, EEG, video, and adjudication data.

The AI deployment package will be version-controlled, checksum-archived, and mounted on a secure institutional server. System downtime, failed inference, and fallback to manual review will be logged. The prospective validation pipeline will be executed in a locked software environment implemented in Python and R. Statistical analysis code will be finalized before outcome analysis and archived as a versioned study record.

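### The primary hypothesis concerns the mean of D_i, but section 2.10 lets the observed outcome data choose the test, and a usual alternative does not test a mean

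*Protocol article*

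**What the plan says.** Section 2.7 (Outcome measures) defines D_i as the average over two raters of raw absolute error minus AI-standardized absolute error. It states the hypothesis in terms of a mean: "The primary analysis will test whether the mean of" D_i differs from zero. Section 2.10 (Statistical analysis) repeats this, saying that the analysis will "test whether the mean participant-level error reduction differs from zero", and then gives the test as "using a paired test appropriate to the empirical distribution".

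Four other statements bear on the point:
- Section 2.10 opens with "All analyses will be prespecified and performed after prospective database lock".
- Section 2.10 fixes the interval method: "Confidence intervals for primary and major secondary metrics will be estimated using participant-level bootstrap resampling".
- Section 2.12 says "Statistical analysis code will be finalized before outcome analysis and archived as a versioned study record".
- Section 2.10 adds a secondary model, "A linear mixed-effects model with participant as a random effect and method and rater as fixed effects", which "will be used as a secondary sensitivity analysis to estimate rater-level effects".

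**The concern.** The hypothesis is fixed in advance, but the test of it is not. Choosing the test from the empirical distribution of D_i is harmless only if every candidate tests the same quantity. The one-sample t-test and the signed-rank test do so when D_i is symmetric. When it is skewed, the signed-rank test targets the pseudo-median (the median of all pairwise averages), which can differ from zero while the mean is zero.

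Two things are at stake. The type I error of a claim about the mean may not be 5%. The p-value may also disagree with the bootstrap interval planned for the same endpoint, leaving two answers to one primary question.

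**Working it through.** **Inputs.** Section 2.9 gives 98 evaluable participants, an SD of 2.5 for the paired differences, a mean reduction of 1.0, two-sided alpha 0.05 and 80% power. The documents give no distribution for D_i, so skewness is an assumption and is varied from 0 to 2.

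**The plan's own figure.** The paired formula gives n = (2.5 × (1.960 + 0.842) / 1.0)² = 49.06, so 50 participants, or 52 with the exact t distribution. The stated 98 matches twice that value, 2 × 49.06 = 98.1, which is the per-group formula for two independent groups. That is a separate and conservative matter. Here 98 is taken as the analysis size; under the planning inputs the t-test then has 97.5% power.

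**Why the target shifts.** Take D = ±2.5 × (G − k)/√k with G gamma of shape k. The mean is 0, the SD 2.5 and the skewness ±2/√k.
- Skewness 1 (k = 4): the pseudo-median of G is half the median of a gamma of shape 8, 7.669/2 = 3.835. So the pseudo-median of D is 2.5 × (3.835 − 4)/2 = −0.21.
- Skewness 2 (k = 1): half the median of a gamma of shape 2 is 1.678/2 = 0.839, giving 2.5 × (0.839 − 1) = −0.40.

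Reversing the skew reverses both signs.

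**Rejection rates with true mean 0, n = 98** (20,000 simulated trials per row; the gated choice uses signed-rank when a Shapiro-Wilk test rejects at 5%, otherwise the t-test):

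| Distribution of D_i | t-test | Signed-rank | Gated choice |
|---|---|---|---|
| Normal | 5.1% | 5.1% | 5.2% |
| Symmetric, t with 5 df | 4.9% | 4.9% | 5.1% |
| Skewness 1 | 5.4% | 13.2% | 13.3% |
| Skewness 1, half-point grid | 5.2% | 11.3% | 11.3% |
| Skewness 2 | 5.7% | 37.5% | 37.5% |

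On a half-point grid at skewness 2, the gated choice rejects in about 31%. At skewness 1 the Shapiro-Wilk test rejects in 95% of trials, so a gate of this kind would nearly always switch. If the analyst simply took the smaller p-value, the error would be 6.1% even for normal data.

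**Direction.** Put 80% of participants at +0.5 and 20% at −2.0. The mean is 0.8 × 0.5 − 0.2 × 2.0 = 0, yet the signed-rank test declares benefit in about 70% of trials. Reverse the signs and it declares harm in 70% and benefit in none. This example has an SD of 1.0 and skewness of −1.5, so it illustrates direction and not a likely size.

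**Secondary mixed model.** Read the model as having a participant intercept only, with four errors per participant (two methods, two raters). Let s² be the residual variance, a the participant-by-method variance and b the participant-by-rater variance. The true variance of the method difference is proportional to s² + 2a; the model's is proportional to s² + (2/3)(a + b). The ratio of model SE to true SE is then:
- a = b = 0: 1.00 (simulated type I error 4.9%)
- a = 1, b = 0, s² = 1: √(1.667/3) = 0.75 (14.2%)
- a = 0, b = 1, s² = 1: √(1.667/1) = 1.29 (1.0%)
- a = 1, b = 2, s² = 0.5: √(2.5/2.5) = 1.00 (5.1%)

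The documents give none of these variances.

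**The case against.** The article condenses a fuller protocol, the SAP is not shown, and the exact test is often named there. Section 2.12 finalizes code before outcome analysis, so a coded selection rule may exist. No rank test or normality check is mentioned, and a test of the mean could be a t-test or a bootstrap test. The bootstrap interval is fixed, so a significant rank test beside an interval covering zero would be visible in the report.

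Much of this stands, and it limits the point. It does not remove it. The article is not silent: it states that the distribution decides. A coded rule would remove analyst discretion, but the test would still depend on the outcome data. The fixed interval would expose a conflict without saying which result decides.

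Three stronger readings are tempting and are not supported:
- **The switch favours the AI.** A reader might infer this from a pattern of rare, large AI errors. Mirroring the skew turns false benefit into false harm. The reference in section 2.5 is the highest credible response, so occasional large raw under-scoring, and hence skew the other way, is also plausible.
- **Error rates near 70% are to be expected.** They arise only in distributions constructed for illustration, with an SD well below the planning value of 2.5.
- **The mixed model's standard errors are wrong.** The description is brief, the variance components are unknown, and the model is a secondary analysis aimed at rater-level effects.

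**Conclusion.** The point holds in a limited form. Section 2.10 makes the confirmatory test depend on the outcome data, which conflicts with its own statement that all analyses are prespecified and with a hypothesis fixed on the mean.

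The consequence is conditional on two assumptions: that the wording leads to a signed-rank test, and that D_i is skewed. With both, at 98 participants and SD 2.5, type I error for the mean is 11–13% at skewness 1 and 31–38% at skewness 2, against about 5–7% for the t-test. Under symmetry there is practically no harm. The direction cannot be stated from the documents.

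The mixed-model remark is a possibility, not a demonstrated error: the method standard error could be too small, too large or right.

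**What to change.** In section 2.10, name the one-sample (paired) t-test on D_i, with its 95% confidence interval, as the primary analysis, and state that no distribution-based switching will occur. Give the participant-level bootstrap interval for the same mean as the robustness check, and report any signed-rank test as descriptive only. This takes two sentences and no extra participants, since the t-test holds its level adequately at 98 even at skewness 2.

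Optional: if the four-row mixed model is to support inference on method, add participant-by-method and participant-by-rater random effects, or use participant-clustered standard errors. It should not be replaced by a model of the rater-level differences, because rater main effects cancel there and the protocol wants to estimate them.

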### Sample size

2.9

The retrospective development sample size will be justified separately from the prospective validation sample size, consistent with current guidance for clinical prediction model and AI model reporting (34, 37, 38). The final development report will state the number of unique patients, the number of assessment episodes, the number of episodes per patient, diagnostic-category frequencies, CRS-R subscale-level distributions, and the number of candidate and retained predictors. The model-development strategy will not rely on a simple events-per-variable rule. Instead, the final feature space and model complexity will be constrained through prespecified feature grouping, training-fold-only feature selection, penalization or tree-complexity limits when applicable, and patient-level nested cross-validation. Learning-curve or resampling summaries will be used to assess whether performance estimates remain unstable as development data are increased.

The prospective validation sample size is based on the participant-level primary endpoint. Assuming a mean participant-level reduction of 1.0 CRS-R point in absolute total-score error after AI-assisted standardization, a standard deviation of participant-level paired differences of 2.5, a two-sided alpha of 0.05, and 80% power, at least 98 evaluable participants are required. Allowing approximately 15% attrition due to unusable EEG, incomplete paired assessments, missing videos, or withdrawal, the planned recruitment target is 120 participants.

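### The only interval method named, the participant-level bootstrap, has zero width for sensitivity or specificity when every reference case is correct, and the percentile type undercovers in small reference groups or at very high accuracy

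*Protocol article*

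**What the plan says.** Section 2.10 (Statistical analysis) sets the interval rule in one sentence: "Confidence intervals for primary and major secondary metrics will be estimated using participant-level bootstrap resampling". The protocol does not say which secondary metrics are major, which type of bootstrap is meant, or what happens when an estimate is 0% or 100%.

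Section 2.7 (Outcome measures) includes among the secondary outcomes "sensitivity and specificity for detection of MCS and emergence from MCS, macro-averaged F1-score, uncertainty-flag performance". Section 2.10 repeats them: "Diagnostic-category agreement will be assessed with weighted kappa, macro-averaged F1-score, sensitivity, specificity, and confusion matrices using the mapping rules in Table 1". It names no separate interval method for these measures.

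Three other statements bear on the denominators:
- Section 2.9 (Sample size) says that "at least 98 evaluable participants are required", and gives no expected split by diagnosis.
- Section 2.2.1 (Inclusion criteria) lists coma, UWS, MCS minus and MCS plus as entry diagnoses. Emergence from MCS is not on that list, although it is a row of Table 1 and a sensitivity target in section 2.7.
- Section 2.4.2 (Assessment workflow) runs the model once on each rater's scores, so each participant contributes two correlated classifications.

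**The concern.** A bootstrap can only redraw what was observed. For a mean error or an intraclass correlation that is usually adequate. For a proportion near 1 in a small group it is not: if no reference case is missed, no resample contains a miss, and the interval shrinks to a single point. When one or two cases are missed, the percentile limits are coarse and often too narrow.

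The error overstates certainty. A model that detects 10 of 10 participants who have emerged from MCS would be reported with an interval of 100% to 100%, when the data are compatible with a true sensitivity of about 70%. In very rare categories some resamples also contain no reference case, so sensitivity is undefined in those resamples and the class F1 that feeds the macro average is degenerate.

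**Working it through.** **The plan's own figures.** The protocol gives no precision figure for sensitivity or specificity, so there is none to reproduce. Its only relevant count is 98 evaluable participants, taken here as stated. (From the stated inputs the paired formula gives ((1.960 + 0.842) × 2.5 / 1.0)² = 49.1, and twice that is 98.1. How 98 was reached is a separate matter and does not affect this point.)

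**Assumptions.** The reference-group size n and the true sensitivity or specificity p are not in the protocol, so both are varied. The main calculation uses one output per participant and the percentile bootstrap.

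**Collapse.** If all n cases are correct, every resample gives n/n = 100%. The chance of this is pⁿ, for example 0.90¹⁰ = 0.349 and 0.95²⁰ = 0.358. The exact (Clopper-Pearson) lower limit for n out of n is 0.025^(1/n): 47.8% for 5 of 5, 69.2% for 10 of 10 and 83.2% for 20 of 20. The bootstrap reports 100% in each case.

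**Coverage.** With x correct out of n, the percentile limits are the 2.5% and 97.5% quantiles of Binomial(n, x/n), divided by n. Coverage is the sum of the Binomial(n, p) probabilities of those x whose limits contain p.

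Worked case, n = 10 and p = 0.90:
- x = 10 gives 1.0 to 1.0, which misses 0.90.
- x = 9, 8, 7 and 6 give 0.7 to 1.0, 0.5 to 1.0, 0.4 to 1.0 and 0.3 to 0.9, which all contain 0.90.
- Coverage is 0.3874 + 0.1937 + 0.0574 + 0.0112 = 0.650.

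| n | p | Chance all correct | Bootstrap coverage | Wilson coverage |
|---|---|---|---|---|
| 5 | 0.90 | 59% | 40% | 92% |
| 10 | 0.90 | 35% | 65% | 93% |
| 20 | 0.90 | 12% | 88% | 96% |
| 20 | 0.95 | 36% | 64% | 92.5% |
| 30 | 0.95 | 21% | 78% | 94% |
| 40 | 0.95 | 13% | 87% | 95% |

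**Where the bootstrap does well.** For p of 0.80, 0.85 and 0.90, coverage is 94.6%, 94.2% and 95.0% at n = 30; 96.4%, 93.9% and 91.4% at n = 40; and 93.8%, 94.1% and 95.7% at n = 50. If the four entry diagnoses were equally common among 98, pooled MCS and its complement would each hold 98/2 = 49. Coverage there is 92%, 94% and 94%, and the chance of collapse at 0.90 is 0.90⁴⁹ = 0.6%. At p = 0.95 coverage is 91%.

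**Two outputs per participant.** In a simulation with an assumed within-participant correlation of 0.7 and p = 0.90, the participant-level bootstrap covered 48% (n = 5), 73% (n = 10), 84% (n = 20), 91% (n = 30) and 93% (n = 50). The pairing softens the problem in the smallest groups but does not remove it. A Wilson interval that treats the 2n outputs as independent is no remedy: at n = 20 it covered 82% at p = 0.80 and 83% at p = 0.90.

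**Empty resamples.** With 2 or 3 reference cases among 98, the chance that a resample contains none is (1 − 2/98)⁹⁸ = 13% or (1 − 3/98)⁹⁸ = 5%.

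**Check of a replacement.** Average the two outputs within each participant and apply Wilson with n equal to the number of participants. Exact enumeration over n = 5, 10, 20, 30, 40 and 50, p = 0.80, 0.90 and 0.95, and within-participant correlations 0, 0.6 and 1 gives coverage between 91% and 99.7%. The lowest value is at n = 10, p = 0.95 and correlation 1, where the method is plain Wilson.

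**The case against.** The strongest reply has four parts.

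First, the rule covers only major secondary metrics, and that word is not defined. The sentence in section 2.10 that explicitly promises 95% intervals names intraclass correlations, mean absolute error, root mean square error and Bland-Altman plots. The sentence with sensitivity and specificity promises none. This stands as a limit on the reading: a reader might infer that the bootstrap is prescribed for every secondary metric, and the text does not say so. But these are named outcomes, and either the bootstrap applies to them or they have no stated interval.

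Second, a reader might infer that denominators of 5 to 40 are this trial's category sizes. They are not in the document. The targets are MCS and emergence from MCS, not five separate categories, and pooled MCS may well be large enough for the bootstrap to work. This stands.

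Third, bootstrap type and boundary handling are commonly left to an analysis plan. That holds for the type, and the coverage figures apply only to the percentile type. The collapse at 100% follows from resampling the observed cases, which the protocol does fix.

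Fourth, confusion matrices are to be reported, so 10 of 10 would be visible. This tempers the consequence: it would be wrong to say that the result would appear with no sign of its uncertainty. The printed interval would still be wrong.

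Resampling by participant is also the right unit for correlated outputs, and nothing here counts against it for the primary endpoint.

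**Conclusion.** The point holds in a limited form. Read to include sensitivity and specificity, the stated rule gives a zero-width interval whenever every reference case is correct. The percentile version also undercovers in groups of about 20 or fewer, or at true values of 0.95 with up to about 40. At 0.80 to 0.90 with about 30 to 50 cases it is close to nominal (91% to 96% in the cases calculated).

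The documents do not support the broader conclusion that the trial's diagnostic-accuracy intervals will fail in general. The clearest risk is sensitivity for emergence from MCS, whose reference count is probably small because it is not an entry diagnosis. Small subgroups are the next risk, if intervals are reported there; section 2.10 does not say that they will be. The figures rest on assumed group sizes, assumed true values and, except where noted, one output per participant. The primary analysis is not affected.

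**What to change.** In section 2.10:
- Keep the participant-level bootstrap for D_i, mean absolute error, root mean square error and the intraclass correlation.
- State whether sensitivity and specificity count as major secondary metrics. For these and other proportions, name an interval that does not collapse at 0% or 100% and that respects the pairing. Options are a Wilson or exact interval for each rater separately, or Wilson on the participant-averaged result with n set to the number of participants. The last needs no estimate of the within-participant correlation. That matters because the correlation cannot be estimated when every output is correct, so an adjustment by estimated effective sample size would fail in exactly that case.
- Print numerator and denominator beside every such estimate.
- State how resamples with no case in a category are handled for macro-averaged F1.

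The cost is a few sentences and a standard function before database lock. Enrolment, data collection and the primary endpoint do not change. The downside is somewhat wider intervals for small categories, and some overcoverage from the averaged Wilson interval when the two outputs are only weakly correlated.
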